### Eligibility criteria

The study population consists of adult patients (> 18 years old) that are approved for cochlear implantation according to standard care criteria. Patients will initially undergo a series of diagnostic tests to assess eligibility for cochlear implantation. These are as follows: a CT scan, a pure tone audiogram/speech test, psychological evaluation, and a consultation by the audiologist and ENT specialist. The Cochlear Implant Team of the UMC Utrecht will assess the work-up results and assess eligibility for cochlear implantation, according to the current clinically applied criteria.

All cochlear implant models will be included in this study. The choice for the cochlear implant model lies with the patient and the CI team of the UMC Utrecht and will not be affected by taking part in this trial. In order to be eligible to participate in this study, a participant must have provided written informed consent authorization before participating in the study. They also must have Dutch written language proficiency and be physically able to undergo a CBCT scan.

A potential participant who is a revision or reimplantation candidate, is unable to understand or sign informed consent, or is pregnant during the trial will be excluded from participation in this study.

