### Sample size

This sample size calculation was based on the primary outcome, R/S migration after 12 months. Due to limited quality evidence on the migration rate for both techniques, an estimation of the migration rates cannot be based on literature; therefore, we base our assumptions on clinical expertise [34, 42, 43]. We consider a migration under 1.0 mm or 1° to be clinically irrelevant. Migration under these cut-off points is within the measurement error margin of the measurement technique of the CBCT scan analysis. A sample size of 51 per study arm reaches 80% power (*β* = 0.8) and a significance level (*α*) of 0.05 with a non-inferiority margin of 1.0 mm. Standard deviation is estimated at 2.0 mm based on the database of Maxwell et al. [43]. In order to cover for possible loss to follow-up estimated at a maximum of 10%, we will include 56 patients per study arm.

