### Randomization and blinding

Patients will be randomly assigned to one of the two study groups with 56 patients allocated in each group. Randomization takes place in the UMC Utrecht-endorsed electronic data capture system Castor EDC. (https://www.castoredc.com/). After giving informed consent, patients will be randomized with an allocation ratio of 1:1 and variable block sizes, with stratification for age (18–50 years, >50 years). Stratification is applied in both study groups. This is a single-blind study, meaning that only participants are blinded for the treatment allocation. The randomization will be done before surgery and patients will not be informed about the allocation. The research team is not blinded. The outcome data will be blindly analyzed. Blinding of the data will be performed by the electronic Case Report Form system used (see section “Data collection plan”). In the event that a revision surgery is necessary for removal or repositioning of the CI, unblinding is permitted. A member of the research team will inform the subject of the allocation.

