#### Statistical analysis primary objective

The main outcome is R/S device migration calculated by analyzing 3D reconstructions of the R/S device, acquired by CBCT scans at baseline and during follow-up. Migration will be reported in millimeters and angle degrees (continuous variables) between the intervention group and the control group at baseline and 3 and 12 months after implantation. Differences between the intervention and control group will be calculated using the unpaired *t*-test or the Mann-Whitney *U* test.

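### Randomisation is stratified by age, but the named primary test ignores the stratum. If age predicts migration this costs a little precision; it does not threaten validity.

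*Protocol article*

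**What the plan says.** Protocol article, Randomization and blinding: "patients will be randomized with an allocation ratio of 1:1 and variable block sizes". The same sentence specifies "variable block sizes, with stratification for age", with strata 18–50 and over 50 years. The Abstract and the flowchart legend also give age as the stratification factor.

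Protocol article, Statistical analysis primary objective: "Differences between the intervention and control group will be calculated using the unpaired" t-test or the Mann-Whitney U test. The three statistical analysis sections contain no age-adjusted or stratified comparison and no confidence interval for the primary outcome. The only decision rule stated there is a p-value below 0.05.

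Protocol article, Sample size: "A sample size of 51 per study arm reaches 80% power", "with a non-inferiority margin of 1.0 mm" and an SD of 2.0 mm. The calculation takes no credit for stratification.

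**The concern.** Stratifying by age balances the arms within each age group. Any difference in migration between younger and older patients therefore largely drops out of the comparison between arms. An unpaired test does not know this: it leaves the between-stratum variance in its error term. If age matters for migration, the estimated standard error exceeds the true sampling variability of the difference, and the test runs below its nominal level.

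In a non-inferiority trial an over-wide interval makes it harder to exclude the margin. Spare power is limited. Losing the allowed 10% from 56 per arm leaves 56 × 0.9 = 50.4, and power at 50 per arm is 0.799 by the noncentral t. Precision that the design has already bought is worth using.

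**Working it through.** **Inputs from the protocol article.** Sample size: 51 per arm, SD 2.0 mm, margin 1.0 mm, alpha 0.05 (sidedness not stated), 80% power. Randomization and blinding: 1:1 allocation, two age strata.

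**Assumed.** R², the share of outcome variance explained by age stratum, is not given, so 0, 0.02, 0.05 and 0.10 are shown. Also assumed: true difference zero, normal outcome with total SD 2.0 mm, equal stratum effect in both arms, balance within strata.

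**Step 1: the plan's own figure.** With one-sided alpha 0.05 the normal approximation gives 50 per arm. The noncentral t gives power 0.799 at 50 and 0.806 at 51, so 51 is reproduced. One-sided 0.025 would need 63 and does not reproduce it. One-sided 0.05 is used below.

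**Step 2: standard errors.** The unadjusted test uses SE₀ = 2.0 × √(2/51) = 0.396 mm. After stratified allocation the true standard error is SE₁ = SE₀ × √(1 − R²), and the adjusted model estimates this value.

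**Step 3: interval width.** The unadjusted 90% half-width is 1.645 × SE₀ = 0.652 mm; the adjusted one is 1.645 × SE₁. The excess width is 1/√(1 − R²) − 1.

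**Step 4: power (normal approximation).** Both tests use the same difference, whose true standard error is SE₁. They differ only in the estimated standard error.
- Unadjusted: Φ[(1.0 − 1.645 × SE₀)/SE₁]
- Adjusted: Φ[1.0/SE₁ − 1.645]

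At R² = 0.05, SE₁ = 0.386. Unadjusted: Φ(0.903) = 0.817. Adjusted: Φ(0.946) = 0.828.

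**Step 5: patient equivalent.** Setting the unadjusted power at n′ per arm equal to the adjusted power at 51 gives n′/51 = [1 + 1.645 × SE₀ × (1 − √(1 − R²))]². At R² = 0.05 this is (1 + 0.652 × 0.0253)² = 1.033.

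| R² | Adjusted half-width (mm) | Unadjusted is wider by | Power, unadjusted | Power, adjusted | Gain (points) | Patient equivalent |
|---|---|---|---|---|---|---|
| 0 | 0.652 | 0% | 0.811 | 0.811 | 0 | 0% |
| 0.02 | 0.645 | 1.0% | 0.813 | 0.817 | 0.4 | 1.3% |
| 0.05 | 0.635 | 2.6% | 0.817 | 0.828 | 1.1 | 3.3% |
| 0.10 | 0.618 | 5.4% | 0.823 | 0.845 | 2.2 | 6.8% |

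**Step 6: check by simulation.** This used 40,000 trials of 102 patients, with 20 assumed to be aged 18–50 and balance within strata. One-sided type I error of the unadjusted t-test was 0.050, 0.049, 0.047 and 0.042 at R² = 0, 0.02, 0.05 and 0.10; the adjusted model stayed between 0.050 and 0.052. Power, unadjusted against adjusted, was 0.802 and 0.802, 0.807 and 0.812, 0.814 and 0.826, and 0.814 and 0.838. This agrees with the table within simulation error and the small difference between normal and t.

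**The case against.** The strongest reply is that nothing promised is lost. The sample size assumes an SD of 2.0 mm and an unadjusted comparison, so the named t-test matches it. Nor do the documents say that age predicts migration; if it does not, adjustment buys nothing. Both points stand, and they limit this to a suggestion about efficiency.

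A second reply is that covariate adjustment is often left to the SAP, which is not shown. An adjusted analysis there cannot be ruled out. But the article names a specific test that leaves out the stratum, so an SAP would have to override that text and not merely fill it in.

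Four stronger readings are tempting, and the documents do not support them:

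- **That the primary test is invalid or could falsely declare non-inferiority.** The error runs the other way: the unadjusted type I error was never above nominal in the simulation.
- **That the trial falls below its planned power because of this choice.** With total SD 2.0 mm, unadjusted power is at least as high with a predictive stratum as without one (0.813 to 0.823 against 0.811). Whether 80% holds under a different sidedness of alpha is a separate question.
- **That adjustment is worth 1/(1 − R²) in patients, or 2%, 5% and 11%.** That ratio suits a covariate not used in the allocation. Here stratification has already removed the between-stratum variance from the estimate and only its standard error is overstated, so the equivalents are 1.3%, 3.3% and 6.8%.
- **That implant model or manufacturer should also be adjusted for, at no cost.** Eligibility criteria does say "All cochlear implant models will be included in this study", but model is not a stratification factor, so leaving it out creates no mismatch with the design. It is also not among the intake data listed under Outcomes, and Data collection plan ties changes to the case report form to a protocol amendment.

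**Conclusion.** The mismatch between stratified allocation and unstratified analysis is real, and its direction is clear: the unadjusted t-test is conservative if age stratum predicts migration. Its size is small over the range examined. It is zero if age explains nothing, and at R² = 0.10 it reaches 5.4% in interval width and 2.2 points of power. R² is an assumption throughout, and the figures rest on one-sided alpha 0.05, SD 2.0 mm and a t-based comparison.

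They do not describe the Mann-Whitney U test. That test gives no mean difference in mm to set against the margin, which is a further reason to prefer a model-based estimate. Because the plan names no interval, the widths refer to the one implied by the t-test.

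This is a worthwhile improvement at almost no cost. It does not call the result into question.

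**What to change.** In Statistical analysis primary objective, replace the choice between t-test and Mann-Whitney U test for the primary comparison. The primary estimate should be the treatment coefficient, in mm at 12 months, from a linear model with arm and age stratum (as used at randomisation). Report it with a confidence interval, robust or bootstrap if migration is skewed, and compare its upper limit (tight pocket minus bony recess) with the 1.0 mm margin. State the confidence level so that it matches the intended one-sided alpha; for the one-sided 0.05 that reproduces 51 per arm, this is a two-sided 90% interval.

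The cost is one degree of freedom out of 100 (102 patients, two arms) and a change of analysis wording, to be made before the outcome data are analysed. Age is listed among the intake data under Outcomes and is needed to randomise, so no new data collection is required.

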#### Trial design

This is a single-blind, non-inferiority randomized controlled trial, with two study arms (Fig. 1). Patients will be randomly allocated into equally sized groups: group A and group B (allocation ratio 1:1). Patients in group A will be operated with the bony recess technique, and patients in group B will be operated with the subperiosteal tight pocket technique. Inclusion in the study will have no consequence for the model or brand chosen by the patient, as is currently standard practice.

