### Statistical analysis

To assess whether continuous variables are normally distributed, histograms and Q-Q plots will be computed. Continues data will be expressed as mean ± standard deviation (SD) when normally distributed, and as median ± interquartile range (IQR) when skewed. Number of cases and percentages will be presented as categorical variables. A *p*-value <0.05 is considered statistically significant. All analyses will be conducted according to the intention-to-treat principle.

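### The trial is sized for non-inferiority on a 1.0 mm margin, but the primary analysis as written is an ordinary between-group test at p<0.05 that never uses the margin

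*Protocol article*

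**What the plan says.** Under Trial design the article states: "This is a single-blind, non-inferiority randomized controlled trial, with two study arms". The Sample size section ties the calculation to the 12-month outcome ("This sample size calculation was based on the primary outcome, R/S migration after 12 months") and gives the planning values: "A sample size of 51 per study arm reaches 80% power", "and a significance level (*α*) of 0.05 with a non-inferiority margin of 1.0 mm", and an SD of 2.0 mm. It does not say whether alpha is one- or two-sided.

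The general Statistical analysis section gives one inferential rule: a p-value "<0.05 is considered statistically significant". The section on the primary objective says migration will be reported in millimetres and degrees, and then: "Differences between the intervention and control group will be calculated using the unpaired" t-test or the Mann-Whitney U test. These same tests are named under the secondary objectives for COMPASS scores and impedance values, which have no margin.

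The margin is given only in the Sample size section. The 1.0 mm or 1° under Primary outcome measure is a cut-off for calling an individual patient's migration relevant. It is not a limit for the difference between groups.

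**The concern.** A non-inferiority trial asks whether the new technique is worse by less than a stated amount. An ordinary t-test or Mann-Whitney U test asks whether the groups differ at all. The two questions have different answers: a p-value of 0.05 or more does not show that the excess is below 1.0 mm, and a p-value below 0.05 does not show that it is above. An ordinary Mann-Whitney p-value does not even give an estimate in millimetres to set against the margin.

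The trial's single confirmatory conclusion is at stake. The article itself says that the safety of the tight pocket is not yet proven. Without a rule tied to the margin, an imprecise result showing no significant difference could be taken as the reassurance that the trial was set up to provide.

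**Working it through.** **Inputs.** From the Sample size section: margin 1.0 mm, SD 2.0 mm, 51 per arm (56 with allowance for loss), alpha 0.05, power 80%. From Trial design: 1:1 allocation. Assumed, because not stated: a true difference of 0 for the sample size, and normally distributed differences.

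**1. Which test do 51 patients per arm belong to?** Normal approximation: n = 2 × SD² × (z_α + z_β)² / margin².
- One-sided 5%: 2 × 4 × (1.645 + 0.842)² / 1² = 49.5, so 50. With the t distribution, power is 79.9% at 50 and 80.6% at 51. The stated 51 is reproduced.
- One-sided 2.5%, or a two-sided 5% test to detect 1.0 mm: 2 × 4 × (1.960 + 0.842)² / 1² = 62.8, so 63 (64 with the t distribution). At 51, power is 70.6%.

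Of these variants, only a one-sided 5% test against the 1.0 mm margin gives 51.

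**2. Which observed differences lead where?** SE = 2.0 × √(2/51) = 0.396 mm, with 100 degrees of freedom.
- Two-sided 5% test of zero difference: non-significant up to 1.984 × 0.396 = 0.79 mm.
- Non-inferiority, one-sided 5%: observed difference at most 1.0 − 1.660 × 0.396 = 0.34 mm.
- Non-inferiority, one-sided 2.5%: at most 1.0 − 0.79 = 0.21 mm.

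Observed differences from 0.34 mm (or 0.21 mm) to 0.79 mm are therefore non-significant without being non-inferior.

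**3. How often does this happen?** Non-central t and simulation, SD 2.0 mm, 51 per arm:

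| True excess, pocket minus recess | Non-significant, two-sided 5% | Margin met, one-sided 5% | Margin met, one-sided 2.5% |
|---|---|---|---|
| 0 mm | 95% | 81% | 71% |
| 0.5 mm | 76% | 35% | 24% |
| 1.0 mm | 29% | 5% | 2.5% |

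If the difference test is read as one-sided 5%, non-significance at a true excess of 1.0 mm is 1 − 0.806 = 19%. At 56 per arm the figures are 25% (two-sided) and 1 − 0.838 = 16% (one-sided).

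Even with no true difference, 17% of trials (one-sided 5% margin test) or 27% (one-sided 2.5%) are non-significant without having shown non-inferiority.

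**The case against.** The strongest reply is that the text is silent on the margin but does not exclude it. The primary-objective section states no null hypothesis and no sidedness; a t-test can be run against a shifted null; and a journal article may leave the confidence level and decision rule to the full protocol or an analysis plan, neither of which was available. This limits the point to what the article says. It does not remove it, because the article does name the primary test and the significance rule, and does so as for outcomes without a margin. If another document holds the margin rule, the article's primary analysis still has to be aligned with it.

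A reader might infer more than the text supports, in two ways:

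- **That a non-significant result will be declared non-inferior.** Nowhere does the article equate p≥0.05 with non-inferiority. The 29% and 19% are error rates of a misreading that the text leaves open, not of a rule it contains. They also depend on sidedness, which is unstated, so both are given.
- **That a harmless difference will be reported as inferiority.** This needs an SD well below the planned 2.0 mm, and the documents give no such figure. At the planned SD the reverse conflict did not occur in 400,000 simulated trials at any of the three true differences in the table: significance needs an observed 0.79 mm, while the margin is met only up to 0.34 mm.

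**Conclusion.** The point holds for the article as written. Design and sample size rest on a test against 1.0 mm, while the stated primary analysis is an ordinary comparison of two groups at p<0.05. That is a mismatch within the document, not merely detail left out. As written, no result leads to a non-inferiority conclusion. The data to be collected would still allow one, so the defect lies in the rule and not in the trial's design.

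At the margin, taking non-significance for non-inferiority would carry a false-conclusion risk of 29% (two-sided) or 19% (one-sided), in place of 5% or 2.5%. These sizes assume normality, SD 2.0 mm and 51 analysed per arm. The mismatch itself depends on none of these. It should be corrected before the data are analysed.

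**What to change.** Keep the existing sentence on the t-test and Mann-Whitney U test for the degree outcome and the 3-month comparison, which would otherwise have no stated analysis. Add, for the primary 12-month comparison in millimetres:

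> *The difference in migration (pocket minus recess) is estimated with its confidence interval. Non-inferiority is concluded only if the upper limit is below 1.0 mm. A non-significant test of zero difference is not evidence of non-inferiority.*

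If the data are skewed, use an interval in millimetres, for example a bootstrap interval for the mean difference, rather than a Mann-Whitney p-value alone.

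State the level. A one-sided 95% limit (upper end of a two-sided 90% interval) matches 51 per arm. If a two-sided 95% interval is preferred, restate the power as about 71%; restoring 80% would take 64 per arm, or 64 / 0.9 = 71.1, so 72 with 10% loss.

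The cost is wording only at the level that matches the sample size, with no new data or patients. At the stricter level it is either a lower stated power or a larger trial.

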#### Statistical analysis secondary objectives

COMPASS questionnaire scores between intervention and control at 3 and 12 months after cochlear implantation will be calculated using the unpaired *t*-test (or the Mann-Whitney *U* test).

Statistical analysis of electrode migration data will be compared in a number of cases and percentages. To calculate any association between electrode migration of ≥ 1 mm and R/S device migration, and between electrode migration and a decrease in speech performance tests, Pearson’s correlation test or a Spearman rank correlation test will be performed. Electrode impedance values will be compared between the groups with the unpaired *t*-test (or the Mann-Whitney *U* test). CVC word score tests (with and without noise) will be compared between the groups with the unpaired *t*-test. Within-group comparisons will be calculated with differences of mean values. A clinically relevant speech performance decrease is a speech performance test score decrease of ≥ 7% when scoring between 30 and 80%, and ≥ 5% when the patients’ scores < 30 or > 80% on the speech performance test, a definition based on clinical experts. Incidence and degree of complications will be reported by means of frequencies.

Participants who withdraw from the study prematurely will be considered lost and will be replaced. Reasons for withdrawal or premature termination will be documented. Potential missing data will be handled using multiple imputation. Complete case analyses will be performed as a sensitivity analysis. All analyses will be performed on an intention-to-treat basis.

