**Methods and analysis:**

This single-blind randomized controlled trial will recruit a total of 112 primary cochlear implantation adult patients, eligible for implantation according to the current standard of practice. Randomization will be performed by an electronic data capture system Castor EDC, with participants block randomized to either bony recess or standard subperiosteal tight pocket in a 1:1 ratio, stratified by age. The primary outcome of this study is the R/S device migration rate; secondary outcomes include patient-experienced burden using the validated COMPASS questionnaire, electrode migration rate, electrode impedance values, speech perception scores, correlation between R/S migration, electrode array migration and patient complaints, assessment of complication rates, and validation of an implant position measurement method. Data will be collected at baseline, 1 week, 4 weeks, 8 weeks, 3 months, and 12 months after surgery. All data analyses will be conducted according to the intention-to-treat principle.

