#### Secondary outcome measures

##### Electrode migration

Electrode array migration is defined as a displacement of the basal electrode outside the cochlea of ≥ 1 mm (i.e., approx. 1 contact spacing). To compare the electrode array migration rate between the two surgical techniques, we will analyze the acquired CBCT scan images following a previously validated method [29, 37]. Electrodes, situated at the level of the round window, will be categorized as extracochlear, since electrodes at this position do not provide adequate stimulation or accurate pitch perception so that they mostly have to be removed from the stimulation map.

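### The planned electrode-migration correlations should use displacement in mm for all patients; if the 1 mm yes/no cut is used, at least about a third of the information is lost under a normal model

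*Protocol article*

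**What the plan says.** The Electrode migration section sets the threshold: "Electrode array migration is defined as a displacement of the basal electrode outside the cochlea of ≥ 1 mm". It glosses this as roughly one contact spacing. For the measurement it says only that "we will analyze the acquired CBCT scan images following a previously validated method"; it does not say that a distance in mm will be stored.

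The section on statistical analysis of the secondary objectives first treats the outcome as a count: "electrode migration data will be compared in a number of cases and percentages". It then names two associations for which a Pearson "correlation test or a Spearman rank correlation test will be performed":

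- "any association between electrode migration of ≥ 1 mm and R/S device migration", where the cut is written into the clause;
- "between electrode migration and a decrease in speech performance tests", where the cut is not repeated.

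The partner in the first association is continuous: the section on the primary objective reports R/S migration in millimetres and degrees. For speech, a binary, clinically relevant decrease is defined, while the CVC scores themselves are percentages measured at 3 and 12 months. The abstract lists "correlation between R/S migration, electrode array migration and patient complaints" among the secondary outcomes. No expected rate of electrode migration is given anywhere.

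**The concern.** Pearson and Spearman coefficients suit two measured or ordered quantities. If one of them is reduced to yes/no, the Pearson coefficient becomes a point-biserial correlation that is smaller than the correlation between the underlying distances, and the Spearman coefficient works on only two distinct ranks. The shrinkage is greatest when the event is uncommon. A 1 mm rule applied to CBCT images implies that a distance is read, so the finer measurement is probably obtainable.

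The abstract and the background give a possible effect on electrode position as one reason to prevent R/S migration. A weakened analysis of that link could produce a non-significant correlation that is then read as reassurance.

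The first clause also has a second possible reading: correlate the mm values, but only among patients who moved at least 1 mm. That would restrict the analysis to a subset of unknown and possibly small size, with a truncated range. The text does not settle which reading is meant.

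**Working it through.** **The plan's own figure.** The only calculated figure is the sample size for the primary outcome: margin 1.0 mm, SD 2.0 mm, alpha 0.05, 80% power, 51 per arm. With a true difference of zero and a one-sided 5% test, the normal approximation gives 2 × (1.645 + 0.842)² × 2.0² / 1.0² = 49.5, so 50. The noncentral-t calculation gives 51, which matches. No figure is given for the correlations, so the evaluable number used here is 2 × 51 = 102.

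**Assumed inputs.** Two inputs are not in the document: the share p of patients exceeding 1 mm (range 5% to 50% shown) and the true correlation (0.30 taken as moderate).

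**Formulae.** Let a normal variable be cut so that a share p lies above the cut, and then be correlated with a continuous partner.

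- Attenuation of the correlation: a = φ(z) / √[p(1 − p)], where z is the normal quantile at 1 − p and φ the normal density.
- Information retained: a². Effective sample size: 102 × a².
- Power, by Fisher's z, two-sided 5%: Φ(atanh(0.30 × a) × √99 − 1.96).

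**Without the cut** (a = 1): atanh(0.30) = 0.3095; 0.3095 × √99 = 3.080; Φ(3.080 − 1.96) = 0.869, so 87%.

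**With the cut, one case in full** (p = 0.20): z = 0.842 and φ = 0.280; a = 0.280 / √0.16 = 0.700; a² = 0.490. The attenuated correlation is 0.210; atanh(0.210) × √99 = 2.121; Φ(2.121 − 1.96) = 0.564, so 56%.

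| Share over 1 mm (assumed) | Attenuation a | Information lost | Effective n of 102 | Power, true r = 0.30 |
|---|---|---|---|---|
| no cut | 1 | 0% | 102 | 87% |
| 50% | 0.798 | 36% | 65 | 68% |
| 20% | 0.700 | 51% | 50 | 56% |
| 10% | 0.585 | 66% | 35 | 42% |
| 5% | 0.473 | 78% | 23 | 30% |

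The loss is smallest at p = 50%. Solving a² = 0.5 gives p = 0.209, so the loss passes half when about 21% or fewer patients exceed 1 mm or, by symmetry, 79% or more.

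**Sensitivity to the correlation.** With a true r of 0.20, power is 52% without the cut and 36%, 29%, 22% or 16% at rates of 50%, 20%, 10% or 5%. With a true r of 0.40 it is 99% without the cut and 91%, 82%, 66% or 48%.

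**Sensitivity to shape.** With lognormal displacement (log-scale SD 0.5 or 1.0) and rates of 5% to 30%, the squared correlation between the indicator and the distance is between 0.406 and 0.608, a loss of about 39% to 59%. The direction is stable, but the size depends on the distribution.

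**The case against.** Several points on the other side stand.

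- **The loss is conditional.** A reader might infer that the cut always discards half or more of the information. It does so only if about 21% or fewer, or 79% or more, of patients exceed 1 mm. The background says only that reported rates vary and that electrode migration seems more frequent than once believed, which fixes no rate.
- **A miss is not shown to be likely.** A reader might infer that the planned analysis would probably overlook a moderate association. At an assumed rate of 20% and r = 0.30 the power is 56%, so detection is still more likely than not, and at 50% it is 68%.
- **The speech clause does not state the cut.** It enters only through the definition in the Electrode migration section.
- **Stored mm values are an inference.** The gloss of the threshold as about one contact spacing, and the classification of electrodes at the round window as extracochlear, would also fit a reading by contact. The measurement method is in cited sources that are not at hand.
- **The tests are not invalid.** Pearson with a yes/no variable is equivalent to a two-sample t-test, and tie-corrected Spearman is equivalent to a rank-sum comparison. The complaint is about efficiency.
- **Small displacements may be partly measurement error.** The document gives no error figure for the electrode reading, so the real gain from mm values may be smaller than tabulated.

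One could add that variable coding is commonly left to an analysis plan. That answers less well here, because the 1 mm cut is written into the sentence that names the test.

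**Conclusion.** The point holds as an improvement to a secondary analysis. The wording for the first association puts a 1 mm cut on one variable before it is correlated with a continuous one; for speech the same follows only if the definition carries over. If the indicator is used, the loss under bivariate normality is at least about 36% of the information. With 102 patients and a true r of 0.30, power falls from 87% to between 68% and 30% over assumed rates of 50% down to 5%. These figures rest on the assumed rate, correlation and normal shape. If the mm values of migrated patients only are meant, the loss takes a different form, restriction to a subset, and cannot be sized from the document.

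A reader might go further and infer that the trial's main conclusion is at risk. It is not: the primary comparison uses R/S migration and its own sample size calculation, and these correlations were never powered.

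**What to change.** State in the analysis text, before the data are analysed, that both correlations use basal electrode displacement in mm for all patients with the relevant scans. Correlate it with R/S displacement in mm and with the continuous change in CVC score between 3 and 12 months, using Spearman's coefficient with a 95% interval. Say which pair of scans each displacement comes from. Add the mm value of the CBCT electrode reading to the recorded data, and keep the 1 mm definition for the descriptive migration rate per arm.

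The cost is a few lines of wording and, if the reading method does not already yield it, one recorded distance per scan comparison. No extra scan or visit is needed. The small downside is that sub-threshold values may carry measurement error, so the gain may fall short of the figures above.
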